**Scientific background**

**Friedreich Ataxia (FRDA)**

Friedreich ataxia (FRDA) is characterized by slowly progressive ataxia with mean age of onset between age ten and 15 years. The prevalence of FRDA is 2/100,000-4/100,000. The carrier frequency is 1/60-1/100. FRDA is the most common inherited ataxia in Europe, the Middle East, South Asia (Indian subcontinent), and North Africa. FRDA is typically associated with depressed tendon reflexes, dysarthria, muscle weakness, spasticity in the lower limbs, optic nerve atrophy, scoliosis, bladder dysfunction, and loss of position and vibration senses. More than 50% of individuals with FRDA have cardiomyopathy, 30% have diabetes mellitus, and about 25% have an "atypical" presentation with later onset, retained tendon reflexes, or unusually slow progression of disease. Individuals with FRDA have identifiable mutations in the Frataxin (*FXN)* gene. The most common mutation, that accounts for more than 96% of individuals with FRDA, is a GAA triplet-repeat expansion in intron 1 of *FXN* which results in a loss of function type mutation. About 4% of individuals affected with FRDA are compound heterozygotes for a GAA expansion in the disease-causing range in one *FXN* allele and an inactivating *FXN* mutation in the other allele. Disease-causing expanded alleles:66-1700 GAA repeats. The majority of expanded alleles contain between 600 and 1200 GAA repeats (Campuzano et al 1996, Durr et al 1996, Filla et al 1996, Epplen et al 1997). Frataxin is required for biogenesis of iron-sulfur cluster (ISC), and therefore for the synthesis of enzymes of the respiratory chain complexes I-III and aconitases. Endocardial biopsies of individuals with FRDA revealed a deficiency of ISC proteins (Rotig et al 1997). Frataxin is also thought to play a role in regulation of mitochondrial iron content. Affected individuals show evidence of abnormal accumulation of mitochondrial iron. However, it is likely that mitochondrial iron accumulation may be a secondary manifestation. Frataxin deficiency leads to reduced antioxidant defense, deficient mitochondrial function, and increased oxidative damage. Affected individuals show deficient ATP production and cellular oxygenation in post-exercise skeletal muscle (Lodi et al 1999, Lynch et al 2002) and defective myocardial energy production (Lodi et al 2001, Bunse et al 2003). Penetrance is complete in homozygotes with typical GAA repeat expansions and in compound heterozygotes for an expansion and another deleterious mutation. However, because of wide variability in the size of pathogenic expanded alleles, and for other unknown reasons, onset can range from before age five years to older than age 50 years. Despite the general genotype-phenotype correlations it is not possible to predict the specific clinical outcome in any individual based on genotype. The remaining variability in individuals with FRDA may be caused by genetic background, somatic heterogeneity of the GAA expansion (Montermini, Richter et al 1997; Sharma et al 2002; Sharma et al 2004), and other unidentified factors. The age of onset, presence of leg muscle weakness/wasting, duration until wheelchair use, and prevalence of cardiomyopathy, *pes cavus*, and scoliosis have all shown statistically significant correlations with GAA expansion size (Durr et al 1996; Filla et al 1996; Monros et al 1997; Montermini, Richter et al 1997). The size of the shorter of the two expanded GAA repeats shows better correlation, accounting for about 50% of the variation in age of onset (Filla et al 1996). Cardiomyopathy is more frequently seen with longer GAA repeat alleles (Durr et al 1996, Filla et al 1996, Monros et al 1997). Isnard et al (1997) found echocardiographic evidence of left ventricular hypertrophy in 81% of those with FRDA with repeat lengths greater than 770 triplets and in only 14% of those with repeat lengths less than 770 triplets. Diabetes mellitus or abnormal glucose tolerance does not show a clear-cut correlation with the size of the GAA expansion. Filla et al (1996) found that individuals with diabetes mellitus tend to have larger repeat lengths; in a larger cohort, however, Durr et al (1996) did not find significant correlation either with the size of the GAA expansion or with disease duration. Despite the lack of correlation with the GAA expansion size, Delatycki, Paris et al (1999) found a correlation between the incidence of diabetes mellitus and an earlier age of onset.

Current treatment of FRDA includes symptomatic therapy and devices, there is no medical treatment available. Antioxidant therapy by free radical scavengers such as coenzyme Q10, vitamin E, idebenone (a short-chain analog of coenzyme Q10), and more recently, mitochondrial-targeted idebenone (MitoQ) have been considered potential therapies for slowing the progression of FRDA.

**FRDA and Erythropoietin**

Erythropoetin (EPO) is a 30.400-dalton glycoprotein that was first recognized to regulate red cell production. In humans erythropoetin is produced by peritubular cells in the kidneys of the adult and in hepathocytes in the fetus. The actions of erythropietin in neuroprotection, independent of changes in erythrocyte numbers, are supposed to be due to two mechanisms. First, erythropoietin can act within the *in vivo* context to reverse vasospasm, protects vascular endothelial cells, and stimulates endothelial progenitor cell mobilization (Heeschen et al., Blood 2003) and thus might increase the regenerative capacity of skeletal muscle. EPO modulates inflammation and recruits stem cells. Second, erythropoietin can act directly on neurons by currently unknown mechanisms. Thus, it is supposed to attenuate the production of damaging molecules such as radical oxygen species (ROS) or glutamate-stimulated excitotoxicity.

In several studies on the *in-vitro* and *in-vivo* effects of rhuEPO we were able to detect beneficial effects of rhuEPO in Friedreich’s ataxia. The lack of Frataxin, the disease causing protein deficiency, is partially reversed during rhuEPO treatment, radical oxygen species are significantly reduced in FRDA patients and clinical effects have been found in a recent long term treatment study over six months (personal communication). Since the pathological cascade in FRDA is not exquisite to the central nervous system, but also involves peripheral nerves and skeletal muscle, we intend to investigate circulating and intramuscular endothelial progenitor cells, neovascularization and oxidative metabolism of skeletal muscle in rhuEPO treated FRDA patients.

**Skeletal muscle in FRDA**

Skeletal muscle is a highly specialized postmitotic tissue with a high-level oxidative metabolism. Involvement of skeletal muscle in FRDA has been related to defects of mitochondrial energy metabolism and increased sensitivity to oxidative stress based on sparse morphological studies of muscle tissue of FRDA patients with the findings of mitochondrial proliferation and iron accumulation and deficits of respiratory chain complex activities (Lodi et al. 2006). Additionally, *in-vivo* studies of skeletal and cardiac muscle using magnetic resonance spectroscopy demonstrated impairment of adenosine triphosphate synthesis of skeletal and cardiac muscle in FRDA (Lodi et al. 1999). The spectrum of morphological and biochemical abnormalities of skeletal muscle in a series of genetically confirmed FRDA patients, however, was not systematically investigated.

Maintenance of adult skeletal muscle and regeneration upon damage is largely dependent on satellite cells, a population of tissue-resident committed myogenic progenitors, located in anatomical cell niches beneath the basal lamina of mature myofibers (Mauro 1961) (Schultz and McCormick 1994). After increased work-load or in response to muscle injury, satellite cells enter a well-defined sequence of activation, proliferation, myogenic differentiation and fusion events to repair or replace damaged muscle fibers (Buckingham et al. 2003). The entry of quiescent satellite cells into the myogenic differentiation program is critically regulated by the paired box transcription factors Pax3/Pax7 (Seale et al. 2000) (Relaix et al. 2005) (Zammit et al. 2006) and myogenic regulatory factors including Myf5, MyoD, myogenin and MRF4 (Tajbakhsh and Buckingham 2000) (Kassar-Duchossoy et al. 2004). Additionally sufficient vascularisation is crucial for the integrity and function of skeletal muscle. Increasing evidence by experimental studies suggests recruitment of bone-marrow derived circulating myogenic and endothelial progenitor cells which colonize skeletal muscle via the peripheral blood and contribute to postnatal myo-vasculogenesis. A subpopulation of primitive hematopoietic progenitor cells (HPCs), defined by the surface molecules CD34 and CD133 (Asahara et al. 1997) (Yin et al. 1997) (Gehling et al. 2000), has been found in adults with high potential to differentiate along myo-endothelial lineages *in vitro* (Pesce et al. 2003) (Torrente et al. 2004) and to contribute to regenerating muscle fibers (Jankowski et al. 2002) (Torrente et al. 2004) and neovascularization *in vivo* (Kawamoto et al. 2006). EPO is a potent stimulus for endothelial progenitor cell mobilization (Heeschen et al. 2003) and exhibits high angiogenic potential (Jaquet et al. 2002) (Urao et al. 2006), thus EPO might improve the regenerative capacity and function of skeletal muscle.

**Contributions from the investigators**

**Studies on the Effect of rhuEPO in FRDA**

**Frataxin up-regulation by human recombinant Erythropoietin**

In a first *in vitro* study we showed that recombinant human erythropoietin (rhuEPO) increases frataxin levels in isolated lymphocytes from FRDA patients. Additionally rhuEPO can significantly increase frataxin levels in primary human cardiomyocytes and cardiofibroblasts and neuronal cells (Sturm et al., 2005). Incubation of primary lymphocytes of FRDA patients showed a significant increase of frataxin-levels.

Since there was no animal model available and rhuEPOs long-term use in anaemic patients in the last two decades, an eight weeks “proof-of-concept” study in 10 FRDA patients was perfomed in order to detect a stable in-vivo up-regulation of frataxin in humans. FRDA patients received 5.000 I.U. rhuEPO three times per week subcutaneously for a time period of eight weeks. Frataxin-levels measured by ELISA revealed a stable and significant rise in 7 out of 10 FRDA patients (Boesch et al., 2007). In addition, established markers of oxidative stress such as urine 8-hydroxydeoxyguanosine (a marker for oxidative mitochondrial and nuclear DNA damage) and serum peroxides were significantly reduced after 8 weeks as compared to baseline.

**Studies of CD34+ and CD133+ hematopoietic progenitor cells in human skeletal muscle**

**Evidence for *in vivo* endothelial and myogenic differentiation of CD34+ and CD133+ hematopoietic progenitor cells in human skeletal muscle**

Using immunohistochemistry and reverse transcriptase-polymerase chain reaction (RT-PCR) we detected mononuclear cells expressing the early hematopoietic progenitor cell (HPC) markers CD34 and CD133 in human skeletal muscle of patients with inflammatory myopathies and normal controls without myopathy, who had a muscle biopsy for the exclusion of malignant hyperthermia. In the context of inflammation numbers of CD34+ and CD133+ mononuclear cells were significantly increased within the endomysial connective tissue contrasting with low numbers of these cells in controls without myopathy, suggesting that along with the infiltrating myelomonocytic cell population hematopoietic progenitor cells are mobilized from the bone marrow into the circulation and recruited to injured muscle to augment repair mechanisms following inflammatory damage. Several CD34+ interstitial cells co-expressed von Willebrand Factor at confocal laser scanning microscopy indicating in-situ maturation of CD34+ HPCs to the endothelial lineage. Occasionally, we observed mononuclear cells co-expressing CD133, CD34and Pax7, a marker of early myogenic differentiation, indicating myogenic commitment of some HPCs.

**Aim of the project**

The function of frataxin is still unknown, but strong evidence supports the concept that is critically involved in mitochondrial function and oxidative metabolism. Our previous studies demonstrate increase of frataxin-levels in lymphocytes of FRDA patients after rhuEPO administration. However, the pathological cascade in FRDA is not exquisite to the central nervous system, but also involves peripheral nerves and skeletal muscle. We therefore intent to investigate effects of rhEPO on circulating and intramuscular endothelial progenitor cells, neovascularization and oxidative metabolism of skeletal muscle in FRDA.

Numbers of circulating CD34 and CD133 hematopoietic progenitor cells will be measured in the peripheral blood by FACS analysis at baseline and bi-weekly throughout the study phase. Muscle biopsy will be performed at baseline and after two months rhuEPO treatment to study effects of EPO on Frataxin expression, numbers of CD34 and CD133 hematopoietic progenitor cells, satellite cells, capillary density and respiratory chain complex activities.

**The aims of the proposed study are**

1) to investigate morphological and biochemical parameters of skeletal muscle systematically, to identify the amount of CD34+ and CD133+ hematopoietic progenitor cells as well as to measure the Frataxin expression in skeletal muscle biopsies of FRDA patients at baseline.

2) to measure numbers of circulating CD34+ and CD133+ hematopoietic progenitor cells in peripheral blood of FRDA patients during treatment with rhuEPO;

3) to study effects of EPO treatment on Frataxin expression, numbers of CD34+ and CD133+ hematopoietic progenitor cells, satellite cells, capillary density and respiratory chain complex activities of skeletal muscle tissue obtained by re-biopsy.

4) Magnetic resonance spectroscopy in skeletal muscle at baseline and study endpoint will be additionally performed to analyze *in-vivo* changes in muscle energy metabolism.

**Study Design**

This is a single centre, non randomized pilot study.

**Number of patients**

5-7 patients

**Inclusion criteria:**

- Age > 18 years.
- Diagnosis of Friedreich Ataxia (genetic and clinical)
- Einwilligungsfähigkeit muss gegeben sein.
- Informed written consent must be given.

**Exclusion criteria:**

- hematocrit greater than 50%
- thrombocytosis
- cancer
- chronic inflammatory diseases
- unstable diabetes mellitus (HbA1c>8%)
- chronic liver disease
- alcohol abuse
- epilepsy
- heart insufficiency (NYHA>2)
- previous thrombo-embolic events
- anti-coagulation
- pregnancy or breast feeding
- iron, vitamin B12 and/or folic acid deficiency
- cardiovascular diseases
- psychiatric disorders
- hypersensitivity to rhuEPO
- participation in different clinical trials

**Patients and Investigations**

Seven adult subjects with definite FRDA will be enroled in this study. Skeletal muscle will be obtained by an open biopsy from at baseline (untreated) and after 2 months of rhuEPO treatment after written informed consent.

Treatment encompasses rhuEPO 3.000 IU (~100 IU/kg KG) three times weekly subcutaneously for 8 weeks.

Specimen from the quadriceps muscle and MR spectroscopy from the contralateral side will be obtained pre- and post rhuEPO treatment.

Frataxin-levels will be assessed in lymphocytes and muscle specimen at baseline and study end-point. Furthermore, FACS analysis of circulating CD34+ and CD133+ cells in peripheral blood will be perfomed bi-weekly. The numbers of CD34+ and CD133+ cells and capillary density per mm2 will be quantified in skeletal muscle at baseline and after 8 weeks EPO treatment.

Biochemically, complex I, II, and III of the respiratory chain in the quadriceps muscle will be evaluated pre-and post treatment.

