**Interventions**

**Treatment**

Human recombinant erythropoietin (rhuErypo) will be applyed three times weekly. The dosage will be 3.00 IU Neo-Recormon (Roche). The appication of the medication will be done by the patient in the gluteal area: In case of iron deficiency (anemia) Fe will be substituted. (z.B. 200 mg elementares Eisen/Tag).

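### The rhuEPO dose is stated inconsistently: 3,000 IU is not about 100 IU/kg per injection in adults, and the treatment section prints 3.00 IU

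*Protocol*

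**What the plan says.** The dose is stated twice in the protocol.

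- *Patients and Investigations*: "Treatment encompasses rhuEPO 3.000 IU (~100 IU/kg KG) three times weekly subcutaneously for 8 weeks". The same section fixes the population: "Seven adult subjects with definite FRDA will be enroled in this study". The inclusion criteria also require an age above 18 years.
- *Interventions, Treatment*: the drug "will be applyed three times weekly", and "The dosage will be 3.00 IU Neo-Recormon (Roche". The same paragraph makes the patient responsible for giving it: "The appication of the medication will be done by the patient in the gluteal area".

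Two other places show how numbers are written. The background has "Erythropoetin (EPO) is a 30.400-dalton glycoprotein". The account of the previous pilot has "FRDA patients received 5.000 I.U. rhuEPO three times per week subcutaneously for a time period of eight weeks". In both, the dot separates thousands.

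The protocol states no body weights, no weight-based dose calculation and no rounding rule.

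**The concern.** There are two faults. The per-kg figure in brackets does not follow from the absolute dose beside it for any usual adult weight, unless it is read as a weekly amount, which the sentence does not say. The treatment section then prints a different number, 3.00 IU, which does not match 3,000 IU on any reading of the dot.

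The dose of the only study drug is what instructions and dispensing labels are drawn from, and here the patients inject themselves. A reader who takes the per-kg figure as the rule would arrive at a dose well above or somewhat below 3,000 IU, depending on whether it is applied per injection or per week. The exposure is also central to reading the results of a pilot in 5 to 7 patients. If it is later cited as about 100 IU/kg per injection, any follow-on work would start from an overstated dose.

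**Working it through.** **Inputs from the protocol.** Dose D = 3,000 IU per injection, three injections per week, 8 weeks, and a gloss of about 100 IU/kg (*Patients and Investigations*; KG is read as body weight). Dose printed in *Treatment*: 3.00 IU.

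**Assumed input.** Body weight W. The protocol gives none, so 50 to 100 kg is shown.

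**Step 1: try to reproduce the gloss.** The weight at which it is exact is W = dose / 100.

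- Per injection: 3,000 / 100 = 30 kg.
- Per week: 3 × 3,000 = 9,000 IU, and 9,000 / 100 = 90 kg.

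The stated figure is therefore not reproduced per injection for adults. It is reproduced per week only near 90 kg.

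**Step 2: what 3,000 IU amounts to, and what a literal 100 IU/kg would require.** The columns are D/W, 100 × W, 3D/W and 100 × W / 3.

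| Weight (kg) | IU/kg per injection | Injection needed if 100 IU/kg is per injection (IU) | IU/kg per week | Injection needed if 100 IU/kg is per week (IU) |
|---|---|---|---|---|
| 50 | 60.0 | 5,000 | 180.0 | 1,667 |
| 60 | 50.0 | 6,000 | 150.0 | 2,000 |
| 70 | 42.9 | 7,000 | 128.6 | 2,333 |
| 80 | 37.5 | 8,000 | 112.5 | 2,667 |
| 90 | 33.3 | 9,000 | 100.0 | 3,000 |
| 100 | 30.0 | 10,000 | 90.0 | 3,333 |

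Between 50 and 80 kg the per-injection reading calls for 5,000 / 3,000 = 1.67 to 8,000 / 3,000 = 2.67 times the fixed dose. The weekly reading calls for 1,667 / 3,000 = 56% to 2,667 / 3,000 = 89% of it. At 70 kg the two readings give 7,000 and 2,333 IU, on opposite sides of 3,000.

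**Step 3: how much the approximation sign can cover.** Allow 20% either way, that is 80 to 120 IU/kg.

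- Per injection: 3,000 / 120 = 25 kg to 3,000 / 80 = 37.5 kg.
- Per week: 9,000 / 120 = 75 kg to 9,000 / 80 = 112.5 kg.

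The weekly reading fits heavier adults but not those of 50 to 70 kg.

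**Step 4: the figure in the treatment section.**

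- Dot as a decimal point: 3 IU, and 3,000 / 3 = 1,000 times too low. Over 8 × 3 = 24 injections this is 72 IU instead of 72,000 IU.
- Dot as a misplaced thousands separator: 300 IU, and 3,000 / 300 = 10 times too low.

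Neither agrees with *Patients and Investigations*. With one zero restored, the figure agrees exactly.

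**The case against.** The strongest reply is that the working dose is not really in doubt. *Patients and Investigations* puts the absolute figure first and the per-kg figure in brackets with an approximation sign. *Treatment* gives only an absolute figure. The previous pilot also used an absolute dose, 5,000 IU. The schedule in the *Synopsis* lists no separate weight measurement. On this view 3.00 IU is a typing slip that few prescribers would act on, and the per-kg figure is a poor aside that instructs nobody. The size of the error also rests on assumed weights and on the per-injection reading. The documents do not show whether either error reached a label. Laboratory tests are scheduled at every visit, and phlebotomy follows above set haemoglobin limits.

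Much of this stands. A fixed 3,000 IU is the likeliest intent, a dropped zero is the likeliest cause, and the monitoring limits the consequence of over-dosing. None of it makes the text correct. The wrong number is in the section that tells people what to give. The section headed for dose modification describes phlebotomy but no change of dose, and that safeguard would not reveal under-dosing as an error in the protocol. A higher intended dose cannot be ruled out from the document either: the pilot's 5,000 IU is itself 100 IU/kg at 50 kg (5,000 / 50).

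**Conclusion.** The concern holds, and the text must be corrected before dosing. As printed, the dose in *Treatment* is wrong by a factor of 1,000 or of 10, depending on how the dot is read. The gloss in *Patients and Investigations* contradicts its own absolute dose on the likelier, per-injection reading: it is exact only at 30 kg and too high by 1.7 to 2.7 times at 50 to 80 kg. On the weekly reading it fits to within 20% from 75 to 112.5 kg and is too low for lighter patients.

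The multiples depend on assumed weights. That the gloss cannot hold per injection needs only that adults usually weigh well over 37.5 kg, and the mismatch between the two sections needs no assumption. The protocol does not settle whether dosing is fixed or by weight, or whether the gloss is per injection or per week.

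**What to change.** State one dose in identical words in *Patients and Investigations* and in *Interventions, Treatment*.

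- If the dose is fixed, give the IU per injection in both places, replace 3.00 IU, and delete the per-kg figure. If an equivalent is kept, correct it and say whether it is per injection or per week.
- If the dose is by weight, give the IU/kg per injection, the weight to be used and a rounding rule, and drop the absolute figure as the instruction.
- Check patient instructions and dispensing labels against the corrected text.

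Which value is right is for the sponsor and its clinicians. The cost is a two-line protocol correction and the label check, with no change to design, sample size or analysis.

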**Synopsis**

| **Assessments and Procedures** | **SC1** | **BL2** | **Visit3** | **Visit4** | **Visit5** | **Visit6** | **FU7** |
| --- | --- | --- | --- | --- | --- | --- | --- |
| **Timepoint (weeks)** |  | **0** | **2** | **4** | **6** | **8** | **10-15** |
| Informed Consent | **X** |  |  |  |  |  |  |
| Medical History | **X** |  |  |  |  |  |  |
| Physical Examination | **X** |  |  |  |  | **X** | **X** |
| Vital Signs | **X** | **X** |  | **X** |  | **X** | **X** |
| **Muscle Biopsy** |  | **X** |  |  |  | **X** |  |
| Muscle MRS |  | **X** |  |  |  | **X** |  |
| FACS | **X** | **X** |  | **X** |  | **X** | **X** |
| Clinical Lab. Tests | **X** | **X** | **X** | **X** | **X** | **X** | **X** |
| Frataxin |  | **X** |  |  |  | **X** |  |
| **SARA** | **X** | **X** |  | **X** |  | **X** | **X** |
| PRO |  | **X** |  |  |  | **X** | **X** |
| AE Assessment |  | **X** | **X** | **X** | **X** | **X** | **X** |
| Concomitant Meds. | **X** | **X** | **X** | **X** | **X** | **X** | **X** |

Abbreviations: SC, screening; BL, baseline; FU, follow-up visit; MRS, magentic resonance spectroscopy ; SARA, Scale for the Assessment and Rating of Ataxia, PRO, patient-reported outcome measures; AE, adverse event

